### Participant recruitment, consenting and retention

Each study arm conducts participant mobilisation to enable HIV testing. Prior to HIV testing, FPD counsellors and SF counsellors will undertake some community mobilisation /demand creation activities through its dedicated personnel. Councillors in each study arm will visit homes in the community and offer HIV testing to each available participant using the inclusion criteria described above. The consenting process will allow collecting contact details including those of next of kin and name of preferred referral clinic for linkage to care follow up. The baseline interview will be conducted soon after a participant signs the consent form while end line data will be collected during participant follow up as described next.

### Follow up

The purpose of participant follow-up in each arm is to collect linkage to care information from clients who tested HIV positive which include whether one is linked to care or not, date linked to care, result of linkage to care, services received (including initiation on antiretroviral treatment) and challenges to linkage to care and treatment, if any. Counsellors will extract and maintain a log of clients’ date of expected follow up – 6 weeks post-testing, clinic name, date of test and identification details including name, gender, age and national registration identity number. Counsellors will visit all referral clinics in the study community and collect these details which are entered into HIV testing registers. The information will be entered onto referral forms issued to the HIV positive clients during post-counselling and entered into the database. Those not yet linked to care will be called telephonically and or visited to encourage them to link with health facilities for treatment. A maximum of six attempts will be made to encourage participants to link with care before they are regarded as lost to follow up. The follow up process will be done within a period of six months post testing.

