## Methods

### Design

The study is a two arm non-randomised community implementation trial with a once off round of post-test follow-up per HIV positive participant to assess linkage to care. Clients will be tested by one of the HIV testing strategies – either by an existing FPD counsellor or a SF HIV counsellor under the sub-contracted model. Each study arm has 19 counsellors conducting CBCT. The overall study design is illustrated on Table 2.

**Table 2 Tab2:** Process flow for the FPD and Social Franchise HTS

Item	Activity	FPD	Social franchise
1. Counsellor Recruitment and contracting	Contract	1. Employed by FPD 2. Normal employment contract 3. Normal payroll contract 4. Work for 8 h a day	1. Unemployed, self-employed or employed elsewhere, not employed by FPD 2. Contracted by franchisee-franchisor contract 3. No restriction on hours, days worked 4. Test >/= 100 people per month 5. Test>/5 HIV + tests per month 6. Link >/= 4 HIV + clients per month
	Remuneration	1. Fixed monthly salary	1. Paid $3.20 per HIV test 2. Paid $8 per HIV + client linked
	Training	Training focussed on: 1. Pre-test, test, post-test, documentation, referral and linkage to care	Training focussed on: 1. Pre-test, test, post-test, documentation, referral and linkage to care 2. business development & management
2. Mobilisation	Community level mobilisation	Community events; flyers; campaigns (e.g. couples counselling); conducting systematic door-to-door mobilization campaigns distributing flyers, and condoms	Community events; flyers; campaigns (e.g. couples counselling); conducting systematic door-to-door mobilization campaigns distributing flyers, and condoms
	Individual level mobilisation	Informing households on the benefits and availability of testing for HIV; scheduling household level testing appointments and/or actively recruiting clients for same day HTS	Informing households on the benefits and availability of testing for HIV; scheduling household level testing appointments and/or actively recruiting clients for same day HTS

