### Control arm - FPD HTS

In order to identify people infected with HIV (PLHIV) and bring them into HIV care, FPD designed and implemented a CBCT programme in 2013 that ran through 2018 [29]. The programme aimed to make significant inroads towards the UNAIDS’s 90–90-90 goal [30] through the alignment with the South African Government’s (SAGs) National Strategic Plan on HIV, STIs and TB (NSP 2012–2016) [31] and the PEPFAR/SA HIV Prevention Strategy [32]. To implement the CBCT strategy, FPD formally advertised and employed counsellors to conduct HTS. The counsellors attended a 10-day training programme covering HTS and linkage to HIV care including documentation, approaching communities, consenting as shown on Table 2. FPD managed counsellors’ daily HTS activities and remunerated them monthly without necessarily pegging the salary to HTS outputs. The client recruitment strategy for testing is described as home-based in which counsellors moved door-to-door recruiting clients in the community. FPD teams, who include a driver/counsellor and at least four other counsellors per team, drive from the office to the communities in the selected study/project sites daily to conduct HIV testing and travel back to the office. Counsellors will test and refer clients for linkage to care. Linkage to care will be confirmed by checking clinic registers and Tier.net, an electronic patient management system used for capturing patient-level data on HTS, pre-ART and ART services. Counsellors will follow up clients for up to six months to ensure that they are linked to care.

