SFs will be remunerated per specific measurable work activities done in order to track progress and measure costing of the project, while also delivering agreed outputs and maintaining the brand. As such, R40^1^ will be paid per HIV test conducted. This amount remunerates a basic package of HTS services to each client tested that includes consenting a client, conducting an HIV test, distributing condoms, providing client tailor made HIV prevention messages and relevant referrals,^2^ screening for TB and STI and subsequently making necessary referrals, documenting the client. A second, and much bigger remuneration, of R100 will be paid for every HIV positive client linked to HIV care and treatment programmes in the health system. This larger amount is aimed at motivating linkage to care which proved challenging for most counsellors implementing CBCT programmes in the country [33, 34]. SFs will be contracted to test a minimum of 100 clients per month. This minimum requirement was determined by calculating the average time required to conduct HIV testing of an average of 5 people per day while allocating time to conduct other duties including mobilisation, documentation and business management aspects. In order to motivate the SFs to study communities to identify and target HIV hotspots [35, 36], it is a contractual requirement to find at least 5 HIV positive individuals in the 100 people tested. This translates to a minimum 5% HIV positivity target in Tshwane district. The target for linkage to care was at least 4 (80%) of the 5 HIV positive clients being linked to care. Consideration was made of the challenges of linkage to care based on FPD’s experience of running the CBCT programme. The project will review the targets upwards once SFs demonstrated delivery of adequate and quality work in order to align to the UN 90–90-90 target for South Africa to link 90% of the HIV positive people identified [30, 37]. Regular (weekly, bi-monthly, monthly, and quarterly) reports, field visits and observations will be made by FPD to monitor program performance and address any challenges. FPD will audit the SFs’ work and provide regular feedback to SFs to assess their progress. The same linkage to care process as in the FPD HTS will be followed by counsellors.

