### Data collection: use of an electronic mobile application (the app)

One of the secondary objectives of the study is to test the effectiveness of a mobile electronic data collection application (the App) in both study groups to collect real time quality data required to assess programme effectiveness and to strengthen linkage to care services. Data will be collected using the App, as well as paper-based tools developed by FPD. The App was designed for this study. The use of the App was deemed to ease the process of linkage to care as client data will be accessible on the South African Government electronic databases and could be accessed by others on the CBCT programme in real time using the Qode Insight system with which to track individual clients’ linkage to care. If a client is linked, the system will capture the name of health facility where a client is linked to care and date of linkage and initiation of care, among other details, through a password-protected online reporting portal. Clients who are lost to follow-up in the treatment cascade will be identified through the Qode Insight system. They will be tracked, and if found, counselled with the aim to reinitiate them on treatment at health facilities. In addition, data captured on the App minimises data entry challenges of accuracy and completeness. Capturing data on paper means that it must be recaptured onto the electronic database support systems (the Bulk Online Capture System or BOCS) that allows the capture of data in situations where the mobile application was not used. The use of the App is therefore expected to contribute towards the success of the entire CBCT programme. All counsellors will be trained for at least one day on using the app. The app has a minimum of 54 variables per participant while a client who tested HIV positive has at least 22 additional variables to complete and those referred for linkage to care will have at least 20 more variables to complete. The app will be completed by the counsellors who administer the interviews. The completion of the app will take place throughout the counselling and testing and linkage process. Every indicator data entry is captured directly onto the application. Participants will be interviewed in vernacular. The app has relevant skip patterns and prompts to suit participants’ various situations and ensure that all relevant questions are entered. The database is managed at FPD by a database developer. Figure 1 shows a picture of a tablet app where client data is entered.

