We anticipate challenges in linkage to care among the SF CBCT. This is because as independent businesses or self-employed, though using an FPD brand, they may not be as well accepted at health facilities as FPD employees would. Although clients usually live within a walkable distance to the local health facilities, some clients may face challenges in accessing these facilities due to shortage of transport money or experiencing stigma making them unable to visit the facility or choosing to visit facilities far away from their locality to minimise stigmatising situations. Training of CHWs will address some of these challenges. In rare circumstances, clients may be offered transport, when available, to access health facilities. The monitoring and management staff will be available to provide support and resolve any conflicts that the SFs face during referral and linkage to care processes. In addition, regular contact with the franchisor through reporting of data, challenges, financial, and commodity fill up visits will enable any challenges to be addressed during project implementation. The use of the App on tablets in a community, sometimes rural or peri-urban communities, raises challenges of internet connection and or gadget battery flat outs or insecurity/theft in high crime areas leading to completing data on paper and later capturing onto the electronic database with possible challenges related to data completeness and real time availability.

The trial will inform on the importance of health information system including gathering, processing, sharing and storage. The success of linkage to care is also hinged on collecting reliable identifying, tracking and locating information. A relationship of trust, which is governed by the consenting process, helps to obtain such private information [44] for follow-up purposes. As observed in large health information systems in South Africa, missing data is a challenge [45, 23]. In our study, missing data may be a result of the interviewer not strictly observing prompts or personnel capturing data from paper-based forms missing some values while capturing. Refresher training and close monitoring of the project will minimise missing data. One of the strengths of the app is that it has prompts that require the counsellor to respond to compulsory questions before proceeding to the next questions.

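### Linkage to care, a primary outcome, is found and recorded by the counsellors, and only the social franchise counsellors are paid per link; the outcome definition should count only record-confirmed links, checked the same way in both arms

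*Protocol article*

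**What the plan says.** **Who collects and enters.** Under Follow up, for both arms: "Counsellors will visit all referral clinics in the study community and collect these details which are entered into HIV testing registers". The counsellor also keeps the log of clients due for follow-up, and the details go onto referral forms and into the database. The data collection section adds: "The app will be completed by the counsellors who administer the interviews", and says this covers the linkage stage.

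**Who is paid for it.** The Intervention arm section sets R40, which "will be paid per HIV test conducted", and then: "A second, and much bigger remuneration, of R100 will be paid for every HIV positive client linked to HIV care". Table 2 gives the dollar figure, "Paid $8 per HIV + client linked", and lists at least 4 linked clients per month among the SF contract terms. Control counsellors have a fixed monthly salary, which the Control arm section describes as not necessarily tied to output.

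**What checks exist.** The Control arm section states: "Linkage to care will be confirmed by checking clinic registers and Tier.net". The Intervention arm section says SF counsellors follow the same linkage process. Table 2 gives both arms the same step of verifying and documenting linkage. The sponsor facilitates verification for SFs and audits their work (Intervention arm section). The Qode Insight system tracks linkage (data collection section). The Discussion refers to site visits, data verification and audit.

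**What counts.** Under Outcomes, linkage is one of four primary outcomes. Its numerator is positive clients successfully linked, and its denominator is positive clients referred. The number linked is also the divisor of cost per person linked, part of a second primary outcome.

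**The concern.** The people who ascertain a primary outcome have a stated financial interest in it in one arm only. A link has to be found before it is counted, and the follow-up section sends counsellors to referral clinics within the study community. The Discussion expects some clients to end up elsewhere, "choosing to visit facilities far away from their locality to minimise stigmatising situations". Tracing such a client takes effort that is paid per link in one arm and not in the other.

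The described checks do not clearly close this gap, for three reasons:

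- Counsellors carry out the shared confirmation process.
- The sponsor's own verification and audit are written for SF work.
- The outcome definition does not say that an unconfirmed link is excluded.

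A record check can expose a false link. It does not make both arms look equally hard for true ones. Any such imbalance enters both the linkage contrast and cost per person linked, and the analysis as described cannot separate it from a real difference in clients reaching care.

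**Working it through.** **1. The plan's own volume.** From Sample size and sampling: 19 counsellors × 100 clients × 24 months = 45,600 per arm, and × 2 = 91,200. Both match the text. The concern does not turn on them; they set the scale.

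**2. Positives per arm.** At the SF minimum of 5 positives per 100 tested: 19 × 5 = 95 per month, so 1,140 at 12 months and 2,280 at 24. Applying this minimum to the control arm is an assumption, because it binds only SFs.

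**3. Strength of the incentive.** At quota, an SF earns 100 × R40 = R4,000 for tests and 4 × R100 = R400 for links. Links are 400 / 4,400 = 9% of pay. One link pays 100 / 40 = 2.5 times one test.

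**4. Unequal detection.** Let true linkage be p in both arms, with detection shares d(SF) and d(control). The false difference is p × [d(SF) − d(control)]. All values are assumptions; the documents give none.

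| p | d(SF) v d(control) | Recorded rates | False difference |
|---|---|---|---|
| 80% | 95% v 85% | 76% v 68% | 8 points |
| 80% | 95% v 90% | 76% v 72% | 4 points |
| 60% | 95% v 85% | 57% v 51% | 6 points |
| 80% | 85% v 95% | 68% v 76% | −8 points |

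**5. False recording in one arm.** If a share f of unlinked clients is recorded as linked, the false difference is (1 − p) × f. At p = 80%: 0.20 × 0.05 = 1 point, 0.20 × 0.10 = 2 points, 0.20 × 0.20 = 4 points. At p = 60% the same shares give 2, 4 and 8 points.

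**6. Against the precision.** The 95% confidence interval half-width is 1.96 × √(2p(1 − p)/n). At p = 80% it is 3.3 points with n = 1,140 and 2.3 points with n = 2,280. If the control arm alone misses 5% of true links at 24 months, recorded rates are 80% v 76% at p = 80% and 60% v 57% at p = 60%. The chance of a falsely significant difference is about 90% and 54%. These figures ignore clustering by counsellor, so they are approximate.

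**7. Effect on cost per person linked.** With a fixed salary, finding 85% of true links multiplies the control figure by 1 / 0.85 = 1.18. For an SF with 4 true links of which 95% are found (3.8), cost per link is 4,000 / 3.8 + 100 = R1,153, against 4,000 / 4 + 100 = R1,100 with all found, a factor of 1.05. The same detection gap therefore distorts both primary outcomes.

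**The case against.** The strongest reply is that linkage is already confirmed from records, in both arms. Table 2 gives both arms the same verifying step, the control section names registers and Tier.net, and the SF section adopts the same process. On that view the missing word in the outcome definition is a drafting gap. Clinic records are not written by the counsellor, audit and unannounced visits add deterrence, and Qode Insight may show links at distant facilities.

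Most of this stands. A reader might infer that linkage is unverified self-report; the documents do not support that. A reader might also infer that links at distant clinics are systematically lost; the coverage of Tier.net and Qode Insight is not stated, so this is not established. False recording is the better-defended route. What remains is that counsellors run the check, the audit is described for one arm, and search effort is not equalised.

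Two further replies also have force. The fee is meant to motivate linkage, and the same follow-up that ascertains status also prompts unlinked clients to attend. Extra effort that gets clients into care is the effect under study, so only finding and recording are at issue. And control counsellors are managed daily and follow clients for up to six months, so they lack a stated financial reason to search, not every reason.

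A condensed article may leave the verification procedure to the full protocol. But who collects linkage, who is paid for it and what the numerator counts are all fixed in this text.

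**Conclusion.** The concern holds in limited form. A primary outcome is collected and entered by counsellors who are paid on it in one arm only, and the confirmation described is not shown to be independent of them or equal between arms. Part of a recorded difference could come from unequal searching, recording or auditing.

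A reader might infer that the bias must favour SF. The documents do not support a direction. Extra finding would favour SF, while auditing SF claims alone would work against it. The Discussion also expects that SFs may be less well accepted at health facilities than the sponsor's employees, which could hinder their access to records.

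The size is unknown. The 8-point figure rests wholly on assumed 80% true linkage and 95% v 85% detection. The calculation shows only that modest gaps would exceed the trial's sampling error at the planned volume. The point deserves correction before the linkage and cost contrasts are interpreted; it does not show that either is wrong.

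**What to change.** In the Outcomes section, count as linked only clients confirmed in Tier.net, a clinic register or the Qode Insight record. Apply the check identically to every client testing positive in both arms, including any not logged as referred. Have it done by the sponsor's data staff who are not paid per link and, where feasible, do not see the arm.

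Keep counsellor-recorded linkage for payment and as a sensitivity analysis. Report match rates and agreement between the two sources by arm.

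The cost is some data-staff time, using record systems and a managed database that the plan already names. True links will be missed where the facility is not covered or the client cannot be matched. This could differ by arm, since SFs choose where and whom to test; the match rates by arm would help show it. Neither client care nor the payment scheme changes.

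### Linkage to care, a primary outcome, is not read at one common time from testing, so how long it is looked for can vary with counsellor conduct and may differ between the arms

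*Protocol article*

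**What the plan says.** Several statements in the protocol article bear on when linkage is observed.

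- **Design:** the trial has "a once off round of post-test follow-up per HIV positive participant to assess linkage to care".
- **Follow up:** counsellors keep a log with a "date of expected follow up – 6 weeks post-testing". They visit the referral clinics and collect the linkage details themselves, and they phone or visit clients who are not yet linked. Then: "A maximum of six attempts will be made to encourage participants to link with care before they are regarded as lost to follow up". The next sentence adds: "The follow up process will be done within a period of six months post testing".
- **Control arm - FPD HTS:** "Linkage to care will be confirmed by checking clinic registers and Tier.net", and "Counsellors will follow up clients for up to six months to ensure that they are linked to care". Salaries are not necessarily tied to output.
- **Intervention arm - SF HTS or SFs:** "The same linkage to care process as in the FPD HTS will be followed by counsellors". SF counsellors receive R100 for each HIV positive client linked.
- **Outcomes:** the linkage rate divides clients who tested positive in the reporting period and were linked by all positive clients referred in that period. Neither 6 weeks nor six months from the test is named. Remuneration cost per person linked is part of the fourth primary outcome.

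**The concern.** Two matters are run together: when counsellors stop encouraging a client, and when that client's outcome is settled. Six months is an upper limit, not a date on which everyone's status is read. Six attempts may be used up quickly or spread over months, so one client may be regarded as lost soon after week 6 while another is pursued to month six. Both stay in the denominator, because it contains every positive client referred. If nobody looks again for the first client, a later linkage goes uncounted.

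The people who decide how the attempts are spaced also collect the outcome data, and they are paid differently in the two arms. An SF counsellor gains R100 from finding a linkage; a salaried counsellor gains nothing extra. A difference in the length or thoroughness of the search would then look like a difference in linkage, and would carry into cost per person linked.

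**Working it through.** **1. What the passages fix when set side by side.** One round (Design), of at most six attempts, within six months (Follow up; Control arm), can be read as nested rules. Even so, they set only an earliest expected contact and a latest limit. The Outcomes section, where a read-out time would be expected, uses the reporting period. No passage requires the registers or Tier.net to be checked for every client at the same time after testing.

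**2. The plan's own figure.** Sample size and sampling gives 91,200 participants in 24 months: 2 arms × 19 counsellors × 100 clients × 24 months = 91,200, which reproduces. Per arm this is 45,600, or 22,800 at 12 months.

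**3. Precision for linkage.** The SF contract targets are 5% positivity and 80% linkage. Applying them to the control arm too is an assumption.

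- Positives per arm: 45,600 × 0.05 = 2,280 at 24 months; 22,800 × 0.05 = 1,140 at 12 months.
- 95% half-width for the difference: 1.96 × √(2 × 0.8 × 0.2 / n) = 2.3 points for n = 2,280 and 3.3 points for n = 1,140. Clustering by counsellor is ignored and would widen both.

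**4. Possible size of an artefact.** The documents give no time-to-linkage data, so the curves are assumed. Both arms have the same true curve, P(T) = 1 − exp(−r·T^k), with r set so that 80% are linked at 26 weeks. Linked by week 6:

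- k = 1 (constant rate): 31.02%, leaving 80 − 31.02 = 48.98 points to link later.
- k = 0.5: 53.84%, leaving 26.16 points.
- k = 0.3 (most front-loaded): 64.54%, leaving 15.46 points.

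Suppose a share f of the clients still unlinked at week 6 is closed in one arm, none in the other, and later linkages of closed clients are never found. The false difference is f × (points still to link):

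| f | k = 1 | k = 0.5 | k = 0.3 |
|---|---|---|---|
| 0% | 0 | 0 | 0 |
| 5% | 2.4 | 1.3 | 0.8 |
| 10% | 4.9 | 2.6 | 1.5 |
| 25% | 12.2 | 6.5 | 3.9 |

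If both arms close some clients early, f is the gap between the two shares. The sign follows whichever arm closes more. With equal closure, or with all clients observed to 26 weeks, the false difference is zero.

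**5. Effect on cost.** With a fixed salary bill, control-arm cost per person linked varies as 1 / (number linked). If the control arm were the one closing 10% early under k = 1, observed linkage would be 80 − 4.9 = 75.1%, and the cost would rise by a factor of 80 / 75.1 = 1.065.

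**The case against.** A reader might infer that follow-up ends at six attempts instead of at any date. The document does not support that. The sentence after the six-attempt rule caps follow-up at six months, the control-arm section repeats the cap, and the SF section adopts the same linkage process. Observation time is bounded in both arms.

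A reader might also infer that effort is paid for in one arm only and that the bias favours SF. Neither follows. Control counsellors are salaried for their work; what only SF counsellors receive is a payment per successful linkage. An SF counsellor keen to be paid may make six attempts quickly and reach the lost category sooner, while a slower salaried counsellor leaves the case open to month six. If payment leads SF counsellors to persuade more clients into care, that is the effect under test.

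The strongest objection is that no passage says a client regarded as lost is coded unlinked. Registers and Tier.net do not depend on the client answering a call, counsellors visit the referral clinics anyway, FPD facilitates verification for SF counsellors, and the data collection section says clients lost in the treatment cascade will be identified through the Qode Insight system and tracked. This stands in part: these routes may recover many late linkages. None of them, however, is tied to a common time or required for every client. Verification guards against false claims more than against linkages nobody looked for.

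Finally, attempt spacing and the coding of lost clients may properly sit in a procedure manual or analysis plan that is not shown. Their absence here is not the point. The article itself states the follow-up rules and the primary outcome definition, and together these leave the read-out time open.

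**Conclusion.** The point holds as a weakness in how a primary outcome is fixed, not as a demonstrated bias. Six months is a ceiling, loss can be declared earlier, and the outcome is defined by reporting period, so the time over which linkage is looked for can differ between clients and between arms. Neither the occurrence nor the direction of a difference is established.

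The size is unknown. The illustration runs from zero to several points, for or against SF; its upper end (12.2 points) needs a 25% gap in early closure together with constant-rate linkage. It rests on assumed curves, 80% linked by 26 weeks in both arms, and closed clients' later linkages never being found. Against a half-width of 2.3 to 3.3 points, even a moderate gap could be mistaken for an effect or hide one. Because the remedy is cheap and uses planned sources, the change should be made.

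**What to change.** - Reconcile the Design, Follow up, Control arm and Outcomes sections on follow-up timing, and leave the contact rule to the programme.
- Separate contact from outcome ascertainment. At six months from the test, which is the plan's own limit, look up every HIV positive client in both arms, including those regarded as lost, in clinic registers and Tier.net. Use the identifiers already collected (Measures lists national ID, referral clinic and client register number) and the same procedure in each arm.
- Count as linked any client whose recorded linkage date falls within six months of the test. Count those not found as not linked. Report loss to follow-up as a process measure only.
- For the 12-month and 24-month analyses, include only clients whose six months have elapsed, or wait until they have.

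The cost is a change of wording, one scheduled look-up per positive client (about 2,280 per arm at the target volumes above) and a data lock up to six months later for the last clients tested. One limit remains: the Discussion expects some clients to attend distant facilities, and any not found in the sources searched will count as unlinked, though under the same rule in both arms.
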